## 5 Trial Flow Chart

2 groups of patients are potentially eligible for the PIONEER trial:

- Cohort A: Patients whose cancers have been deemed to be operable by the Multi-Disciplinary Team (MDT) with tumour excision planned for the next 2-6 weeks
- Cohort B: Patients with early or locoregionally advanced breast cancer planned for primary endocrine therapy either in lieu of tumour excision or as neoadjuvant therapy before tumour excision - such patients must begin PIONEER trial therapy prior to starting any other endocrine therapy.

For all patients who consent to enter PIONEER and are planned for tumour excision, a date for tumour excision should be booked prior to randomisation. The date of tumour excision will determine when the patient should start treatment, as the day of tumour excision should coincide with Day 15 ( $\pm \leq 4$  days) of treatment.

For patients who consent to enter PIONEER but are planned for primary endocrine therapy, the date the patient should start trial treatment must be as soon as it is feasible.

Patients will be stratified according to their baseline characteristics of histological tumour grade (1,2,3), ductal vs. lobular subtype, and intensity of ER staining on IHC of their initial, diagnostic core biopsy. In terms of ER status, patients will be stratified on the basis of the Allred ER score (3-6 moderate, 7-8 strong). This will allow even distribution of these characteristics between the three randomized arms.

**Figure 1.**

[figure not shown]

**Treatment in all arms A/B/C will be for 15 days ( $\pm \leq 4$  days if required).**

[figure not shown]

## **6 Introduction**

### **6.1 Background**

Breast cancer is the most common cancer in women worldwide, and the second most common cancer overall, with more than 1,676,000 people newly diagnosed in 2012 (25% of all female cancer cases and 12% of the total) [1]. Although advances in screening, surgical intervention, radiotherapy and systemic therapies have improved survival, worldwide approximately 522,000 women died as a result of their breast cancer in 2012 [2].

Breast cancer is a heterogeneous disease and there are many ways to classify it, including using traditional histopathological features, immunohistological and molecular classifications [3]. Around 75% of breast cancers are defined and driven by Oestrogen receptor alpha ( $ER\alpha$ ) transcriptional activity. A number of established endocrine treatments already exist, including Selective Oestrogen Receptor Modulators (SERMs) such as tamoxifen, Selective Oestrogen Receptor Downregulators (SERDs) such as fulvestrant, and Aromatase inhibitors (AIs) such as Letrozole, anastrozole (both non-steroidal) and exemestane (steroidal). However, clinical outcomes vary considerably, and a proportion of women with early breast cancer driven by  $ER\alpha$  transcriptional activity develop drug resistance, and relapse with incurable, metastatic disease. There is an urgent need for better treatment strategies.

## **7 Rationale for Trial**

### **7.1 Data from non-clinical trials**

It has been known for many years that Oestrogen receptor (ER) directly induces expression of the Progesterone Receptor (PR) in normal and malignant breast epithelial cells, so that these steroid receptors commonly co-localise. Historically, the accepted explanation was that PR-positivity was a passive consequence of a functional ER, and PR was established as a biomarker of ER functionality in breast cancer [4]. However in recent years, the [name] laboratory (Cambridge Institute, Cancer Research UK) has published preclinical findings exploring ERfunction in breast cancer, providing new insights into progestogen action and functional 'cross-talk' between ER and PR in breast cancer [5].

These preclinical discoveries have provided an alternative explanation to the previous over-simplistic assumption that PR is just a passive consequence of an active ER. In fact, PR can be the cause and not the consequence of altered ER activity.

In the presence of agonist ligands, progesterone-activated PR causes rapid redistribution or sequestration of  $ER\alpha$  chromatin binding sites in breast cancer cells, resulting in a unique gene expression program that is associated with a good clinical outcome, via inhibition of  $ER\alpha$ -mediated transcriptional activity and the oestrogen-mediated proliferative response (Figure 2). Thus, PR functions as a molecular rheostat to control  $ER\alpha$  chromatin binding and transcriptional activity, with important implications for prognosis and therapeutic interventions.

This functional 'cross-talk' between  $ER\alpha$  and PR was explored preclinically by the demonstration that progesterone inhibited oestrogen-mediated growth in primary  $ER\alpha$ + breast tumour explants and  $ER\alpha$ + cell line xenografts [5]. In both MCF-7 and T-47D xenograft models, progesterone alone antagonized oestrogen-induced tumour

[figure not shown]

formation, as did tamoxifen alone. However, the combination of tamoxifen and progesterone had the greatest tumour inhibitory effect.

The potential clinical significance of exploiting this interaction between ER and PR signaling in breast cancer affords the possibility that the addition of a progesterone agonist might enhance the anti-proliferative effect of anti-oestrogen therapies and therefore prove a more effective combination therapy.

**Figure 2. [6]**

### A) Old Model

PR status as a passive consequence of ER function

[figure not shown]

### B) New Model

PR actively influences ER binding sites and function

i) ER function in presence of oestrogen alone

[figure not shown]

ii) ER function in presence of oestrogen plus progesterone

[figure not shown]

[figure not shown]

## **7.2 Clinical Data**

### **7.2.1 Efficacy and tolerability**

A wealth of data already exists confirming the clinical benefit of the addition of Megestrol acetate, a semi-synthetic derivative of progesterone, as a single agent in ER+ breast cancer. Overall, 9 trials have reported survival benefit from treatment with Megestrol acetate in ER+ metastatic breast cancer. Older trials have demonstrated that the benefits of Megestrol acetate are comparable to tamoxifen as first line therapy [7-9]. More recently, Megestrol acetate was found to be efficacious in patients with ER-positive metastatic breast cancer after Aromatase Inhibitor (AI) treatment failure [10]. In this single arm Phase II trial, 48 postmenopausal women were treated with Megestrol acetate 160mg daily. The treatment was well-tolerated, and yielded a clinical benefit rate of 40%, with a median duration of 10 months.

Combination treatment with Megestrol acetate and tamoxifen has previously been found to be a tolerable combination in a randomised comparison of the effects of tamoxifen, Megestrol acetate, or tamoxifen plus Megestrol acetate (11). The combined treatment did not result in a higher response rate, however tamoxifen, as opposed to an AI, was used in a post-menopausal population with metastatic (not early) breast cancer, in a trial that was halted prematurely due to poor patient accrual.

A primary rationale for conducting PIONEER, in addition to seeking an increased anti-proliferative effect, is to help decide whether or not there is value in conducting a larger follow-on adjuvant trial investigating the longer term benefit of the combination of an AI +/- Megestrol acetate, and if so, at what dose of Megestrol Acetate (40mg vs. 160mg).

A second important rationale for a larger adjuvant trial of combination therapy, is to potentially improve the quality of life of women taking anti-oestrogens, at a time in which the intensity [12] and duration [13] of adjuvant endocrine therapy is increasing. The use of low dose progesterone as a supportive therapy has been shown to completely and rapidly ameliorate anti-oestrogen therapy-related hot flushes in 75-85% of patients [14]. This could hopefully prevent patients from prematurely ceasing their adjuvant endocrine therapy thereby improving clinical outcomes.

The efficacy of Letrozole as a single agent has been well established, supporting its current registered use in the following settings:

- Adjuvant and Neoadjuvant treatment of postmenopausal women with hormone receptor positive early breast cancer
- Extended Adjuvant treatment of Early Breast Cancer
- First and Second-Line Treatment of Advanced Breast Cancer

### **7.2.2 Concept of short-term pre-operative treatment**

Short-term preoperative 'window' trials of 2-4 weeks treatment are a validated strategy offering rapid and cost-efficient proof-of-concept for novel treatment approaches by assessing the direct effects of the trial treatment on tumour tissue. These trials allow access to tumour tissue before and after treatment, providing critical insight into differences in activity and mechanisms between agents, the optimal patient population,

[figure not shown]

influence of the tumour biology on sensitivity, and molecular mechanisms of response or resistance.

Multiple trials in the neoadjuvant setting have demonstrated the utility and validity of changes in Ki67 as a predictor of benefit from treatment and of long-term outcome. In the neoadjuvant IMPACT trial, suppression of Ki67 at 2 weeks was greater with anastrozole than with either tamoxifen or the combination of anastrozole plus tamoxifen [15-17], mirroring the results of the much larger adjuvant ATAC trial without the requirement of a long follow-up [18].

Although Ki67 measurements in preoperative trials cannot replace the need for adjuvant trials with clinical endpoints, they can be highly instructive in selecting or rejecting candidate approaches for phase III trials, and defining the most appropriate patient populations. Over recent years, the perioperative window setting of this trial together with the incorporation of primary biological endpoints has been established in the UK as a new approach for breast cancer research. The POETIC trial, a UK NCRN phase III randomised clinical trial with approximately 4000 patients, is currently testing prospectively whether short-term perioperative endocrine therapy with an AI followed by standard adjuvant therapy can improve outcome in postmenopausal women with ER-positive breast cancer. It is also testing whether the proliferation marker Ki67, as measured by immunohistochemistry (IHC) after 2 weeks of AI therapy, will predict for relapse free survival and whether molecular profiling 2 weeks after starting endocrine therapy predicts better for long-term outcome than at diagnosis.

## **8 Trial Design**

### **8.1 Statement of design**

This is a three arm, open-label, multicentre, randomized, window of opportunity, phase II trial which will evaluate the effects of 15 days (+  $\leq 4$  days) preoperative therapy with Letrozole, or Letrozole plus low dose Megestrol acetate (40mg), or Letrozole plus high dose Megestrol acetate (160mg) in postmenopausal women with newly diagnosed, ER-positive, HER2-negative, invasive primary breast cancer of at least 1 cm size.

### **8.2 Number of Centres**

Patients will be recruited from surgical or oncology clinics with approximately 15 participating UK centres.

### **8.3 Number of Subjects**

A total of 189 evaluable patients are required.

Evaluable patients are defined as eligible patients who have completed at least 13 (or 80%) of the full 15 Day (+  $\leq 4$  Days) trial dosing schedule. It is anticipated this will require approximately 10% more patients to be randomised, to account for patients that may not be evaluable.

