#### 9.4.1 Discontinuation

Patients should discontinue trial treatment in the following circumstances and this should be reported in the End of Trial Medications Case Report Form (CRF):

1. If the Investigator decides that the patient should be discontinued from the treatment at any point due to an inter-current illness or if continued participation in the trial will result in delay to planned tumour excision.
2. Any CTCAE Grade  $\geq 3$  drug related toxicity which does not resolve to Grade 1 or less within 72 hours (except where supportive measures exist to control the toxicity which had not been adequately instigated at the time of the AE, e.g. antiemetics for nausea and vomiting or anti-motility agents for diarrhoea).
3. If the patient withdraws from the trial, refuses baseline core biopsy (only applies when diagnostic tissue is not available), opts to discontinue the treatment or chooses not to comply with trial procedures.
4. If the patient's disease is progressing while on trial treatment.

Patients who have been discontinued from the trial treatment and are experiencing ongoing toxicity from Letrozole and/or Megestrol acetate will be followed up as clinically indicated until the toxicity resolves to Grade 1, or less. Patients who have completed the minimum 13 days of treatment (or  $\geq 80\%$  days of dosing if 16 to 19 days of treatment) prior to developing toxicity will continue to attend scheduled follow ups and procedures (unless decided otherwise by the clinician) and their samples/data will be used for analysis.

However, patients who do not complete at least 13 days of the full 15 day pre-operative window dosing schedule (or  $\geq 80\%$  days of dosing if 16 to 19 days of treatment) won't be considered evaluable for the primary endpoint. For patients whose treatment is extended beyond 15 days (up to 19 days), the minimum number of days in which the patient should dose with trial treatment must be greater than 80% of the full treatment window e.g. for 19 days of treatment a minimum of 15 days of study drug must be taken. These patients' samples and data will be retained and may be used for analysis of the secondary and exploratory endpoints. Patients whose treatment is scheduled for 13 days must complete the full treatment window to be evaluable for the primary endpoint (i.e. no treatment doses can be missed).

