### **11.2 Maximum duration of treatment of a patient**

Treatment in all three arms should be continued until tumour excision and/or core biopsy on day 15 (+ ≤4 days) unless there is evidence of unacceptable toxicity, progression or the patient requests to discontinue. Treatment can be planned for 13-14 days if exceptional circumstances mean that tumour excision or Day 15 biopsy can not be scheduled on Day 15 (+ ≤4 days).

In exceptional circumstances where tumour excision is delayed beyond the planned 15 day treatment period, we allow treatment to be continued for up to an additional 4 days.

Should patients experience significant AEs that could potentially impact on the operability, Megestrol acetate should be discontinued permanently whereas Letrozole should be continued until breast tumour excision is performed. If breast tumour excision cannot be performed on day 15 (+ ≤4 days) patients will be required to undergo an additional core biopsy on day 15 (+ ≤4 days) to assess the effect of the trial treatment.

[figure not shown]

Following the 19 days of study treatment, in the event of surgical delay beyond this time, patients may choose to continue treatment with Letrozole alone until the day of tumour excision.

Patients will be excluded from the final analysis if they do not complete at least 13 of the full 15 day pre-operative window dosing schedule, necessitating recruitment of an additional patient.

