## **13 Evaluation of Results (Definitions and response/evaluation of outcome measures)**

### **13.1 Trial Outcome Measures**

#### 13.1.1 Primary efficacy outcome measure

Change in tumour proliferation measured by Ki67 immuno-histochemical assessment (%) at baseline compared to Day 15 (+  $\leq 4$  days).

Ki67 expression will be measured centrally, blinded with treatment allocation, using formalin-fixed, paraffin embedded histopathology sections of the tumour tissue specimens taken at baseline and at Day 15 (+  $\leq 4$ ) days. Additional analyses will also be done on the tumour biopsy specimens taken at breast tumour excision (or the additional research biopsy if tumour excision is not performed on Day 15 +  $\leq 4$  days). IHC for the Ki67-proliferation associated antigen will be carried out on 3-4  $\mu\text{m}$  sections of the routinely processed material following heat mediated antigen retrieval and with the appropriate primary antibodies.

The tumour-cell Ki67 antigen labeling index will be recorded following the

[figure not shown]

recommendations from the International Ki67 working group [19]. Sections from the diagnostic or baseline core biopsy, Day 15 (+  $\leq 4$ ) tumour biopsy/post-surgical specimen will be stained for Ki67. Tumour cell nuclei showing any intensity of staining will be regarded as positive. The stained slide will be reviewed at low power and representative high power fields (x40) will be selected for counting; if there are clear areas with an increased proportion of cells staining (hot spots) these will be included in the count. One thousand tumour cell nuclei will be counted; if there are less than 1000 tumour cells in a biopsy a minimum of 500 will be counted. If there are less than 500 cell nuclei then further sections will be stained at a depth of 25 $\mu$ m and counted until the minimum number of cells is reached. Ki67 will be scored as the percentage of tumour nuclei staining. The investigators analyzing Ki67 will be blinded as to treatment allocation. Ki67-response is defined as a 50% or higher fall in Ki67 expression.

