## **14 Statistics**

### **14.1 Statistical methods**

The primary outcome measure is the change in tumour proliferation measured by Ki-67 immuno-histochemical (IHC) assessment (%) at baseline and on day 15 (+  $\leq$ 4 days). The standard t-test will be applied for the primary comparison between Arm A vs Arm (B+C) based on evaluable patients.

The primary analysis for the primary endpoint will be based on the evaluable population (defined as eligible patients who have completed at least 13 [or 80%] of the full 15 Day [+  $\leq$ 4 Days] dosing schedule).

Adverse events will be summarized for the safety population (defined as all patients who have received at least one dose of protocol treatment) using frequency tables and compared using the Wilcoxon Mann-Whitney test or Kruskal Wallis test. All other secondary outcomes will be summarised using the summary statistics and compared between arms using t-test, ANOVA, Wilcoxon Mann-Whitney test or Kruskal Wallis test where ever is appropriate. A comprehensive statistical-analysis plan will be prepared before any analysis is performed.

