### **14.4 Criteria for the premature termination of the trial**

Patient recruitment will continue until the target of 189 evaluable patients has been reached.

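### The evaluable set is defined by doses taken, so the 189 target can fill with patients who have no Ki67 pair, and randomised patients who do have one can be dropped

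*Protocol*

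**What the plan says.** **Who counts as evaluable.** Section 8.3: "Evaluable patients are defined as eligible patients who have completed at least 13 (or 80%) of the full 15 Day" (with up to four extra days allowed). Section 14.1 repeats this and adds: "The primary analysis for the primary endpoint will be based on the evaluable population". Section 14.5, whose heading concerns missing or spurious data, restates the dosing rule and puts everyone who meets it into the final analyses.

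**What the endpoint needs.** Section 13.1.1 measures Ki67 "using formalin-fixed, paraffin embedded histopathology sections of the tumour tissue specimens taken at baseline and at Day 15". Both specimens are therefore required to compute a change.

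**What is counted on that definition.** Section 14.2 requires 189 evaluable patients (47, 71 and 71) and allows 10% for patients who may not be evaluable, giving about 210 randomised. Section 14.4: "Patient recruitment will continue until the target of 189 evaluable patients has been reached".

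**What happens to under-dosed patients.** Section 9.4.1 says that they "won't be considered evaluable for the primary endpoint", but that their "samples and data will be retained and may be used for analysis of the secondary and exploratory endpoints". Section 11.2 goes further: "Patients will be excluded from the final analysis if they do not complete at least 13 of the full 15 day" pre-operative schedule, and an additional patient is then recruited. Section 11.10 also excludes them from the final analysis. For adverse events that could affect operability, section 11.2 states: "Megestrol acetate should be discontinued permanently whereas Letrozole should be continued until breast tumour excision is performed". Section 9.3 says that the trial is open label, with the histopathologist blinded.

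**The concern.** There are two separate problems.

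1. **The count does not track the outcome.** A patient who takes 13 doses but has no readable Day 15 sample is evaluable by every definition in the protocol, counts towards 189 and helps to close recruitment, yet contributes nothing to the t-test. Such cases are foreseeable. A separate core biopsy is something that patients are asked to undergo (10.3.3). No samples are taken after consent is withdrawn (9.4.2). Section 13.1.1 does not say what happens if further sections still yield fewer than 500 nuclei. Any such patient takes the analysed number below the one that the power claim needs.

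2. **Randomised patients who have the outcome can be removed.** Dosing is a post-randomisation event. Arm A takes one drug and Arms B and C take two, and stopping megestrol alone is possible only in B and C. Exclusion rates can therefore differ by arm, and those excluded may differ in Ki67 response from those kept. Blinded reading protects the measurement but not entry into the analysis set. No primary-endpoint analysis of all randomised patients with a pair is named. The conclusion sought in section 14.2 is about all patients, and section 7.2.1 says that the trial will help to decide on a larger adjuvant trial.

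**Working it through.** **Inputs (section 14.2).** Mean Ki67 reduction 66% in Arm A and 77.5% in Arms B+C, so the difference is 0.115; SD 0.242; one-sided alpha 0.025 for all patients; target power 80%; allocation A:(B+C) = 1:3; 189 evaluable, that is 47 versus 71 + 71 = 142; 10% allowance.

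**Step 1: reproduce the plan's figures.**
- Standard error = 0.242 × √(1/47 + 1/142) = 0.0407.
- Signal = 0.115 / 0.0407 = 2.82.
- Noncentral-t power at 47 versus 142 = 80.2% (normal approximation 80.6%). The smallest 1:3 design reaching 80% is 47 + 141 = 188.
- 189 / 0.90 = 210.

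The stated 189 and 210 both reproduce, and 189 sits almost exactly on 80%.

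**Step 2: dose-evaluable patients without a pair.** The protocol gives no rate, so the missing share m is an assumption. Analysed numbers are 47(1 − m) and 142(1 − m), rounded. The last column is 189 / 0.90 / (1 − m), rounded up: the number to randomise if a patient must meet the dose rule and also have a pair.

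| m | Arm A vs B+C | Power | Randomise |
|---|---|---|---|
| 0 | 47 vs 142 | 80.2% | 210 |
| 5% | 45 vs 135 | 78.4% | 222 |
| 10% | 42 vs 128 | 75.7% | 234 |
| 15% | 40 vs 121 | 73.6% | 248 |

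The PR-positive comparison (difference 0.14, 37 versus 112) starts at 85.8% and falls to 83.8, 81.7 and 79.3% at the same rates. The lack of slack therefore concerns the all-patient comparison.

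**Step 3: what differential exclusion could do (illustration).** Assume that 10% of B+C and none of Arm A are excluded, and that those excluded have a Ki67 fall smaller by g than those kept.
- Overstatement of the B+C mean = 0.10 × g.
- One-sided error when there is no true difference among all randomised = 1 − Φ(1.96 − overstatement / 0.0407).
- g = 10 points: 1 point of bias; 1 − Φ(1.96 − 0.246) = 4.3%.
- g = 20 points: 2 points of bias; 1 − Φ(1.96 − 0.491) = 7.1%.

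If g has the opposite sign, the bias works against the combination.

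**Step 4: cost of analysing as randomised.** Take 210 patients, all with a pair (52 versus 158), with 10% of B+C under-dosed and keeping a fraction f of the added effect. The diluted difference is 0.115 × (0.9 + 0.1f).

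| f | Difference | Power, 210 pairs | Power, 5% of pairs missing (50 vs 150) |
|---|---|---|---|
| 1 | 0.115 | 84.1% | 82.5% |
| 0.5 | 0.109 | 80.3% | 78.6% |
| 0 | 0.1035 | 75.9% | 74.1% |

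**The case against.** **Missing pairs are partly controlled.** Section 16 makes both specimens mandatory. Refusing a needed baseline biopsy leads to discontinuation (9.4.1). Too few nuclei triggers further sections (13.1.1). Section 11.2 requires a core biopsy when excision cannot be done on time. This stands as a reason to expect a modest missing rate. It does not tie the pair to evaluability, and with 80.2% power even a modest rate takes the trial below 80%.

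**The dose-defined set is a deliberate choice.** In a phase II window trial whose objective concerns 15 days of treatment, an analysis of treated patients has a rationale, and preferring an as-randomised set is partly judgement. That is fair, and it supports keeping the dose-defined set as a reported analysis. It does not support having no as-randomised analysis beside it. A pair-based set is itself selected after randomisation, so it reduces the problem without removing it.

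**Stronger readings that the protocol does not support.** A reader might infer three further things.
- *That the exclusions must favour the combination.* Nothing shows that patients who stop early respond worse. Exclusions driven by toxicity could remove good responders.
- *That the error rate could reach about 16%.* This needs a 4-point bias, that is a 40-point gap in 10% of B+C with no Arm A exclusions. With no true megestrol effect, stopping megestrol cannot itself lower the fall; under the planned effect it forfeits at most 11.5 points. A gap of 20 to 40 points would also shrink the as-randomised effect to 9.5 to 7.5 points, with power of about 64 to 45% at 189. One cannot assume the large bias and a small dilution cost together.
- *That dropping under-dosed patients with a pair costs power.* It need not: adding them back gives 75.9 to 84.1% (step 4). The certain power loss comes only from counting patients without a pair.

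**The tissue may not exist.** Section 9.4.1 continues scheduled procedures for patients who reached the minimum dosing before toxicity. For those below it, the section says only that samples are retained. The analysis can therefore use every available pair, but not every randomised patient.

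**Conclusion.** The concern holds, as something that should be fixed.

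The firm part is the counting rule. The protocol itself fixes it in several sections, so it is not detail left to the SAP, and it under-delivers the stated 80% as soon as any dose-evaluable patient lacks a pair. The size depends on a missing-pair rate that the protocol does not state: a loss of about 2 points of power at 5% missing, 4 to 5 at 10%, and 6 to 7 at 15%.

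The second part is a real exposure to selection bias of unknown direction and size. The 1 to 2 points of bias, and error of about 4 to 7%, illustrate one assumed scenario and are not estimates.

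Sections 9.4.1, 11.2 and 11.10 also disagree on whether under-dosed patients leave the primary endpoint only or the final analysis altogether.

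**What to change.** 1. **Count the outcome.** In sections 8.3, 14.2 and 14.4, count patients with an assessable Ki67 at baseline and Day 15 towards 189, and let the 10% allowance cover missing pairs (210 × 0.90 = 189 pairs). If randomisation stays near 210 and more pairs than that are expected to be lost, restate power at the pairs expected. If the dose rule is kept as well, the last column of the table in step 2 gives the numbers to randomise.
2. **Analyse as randomised.** Analyse all randomised eligible patients with a Ki67 pair in their assigned arm, preferably as the primary analysis with the dose-defined set as sensitivity. At minimum, prespecify it and report it beside the dose-defined result.
3. **Reconcile** sections 9.4.1, 11.2 and 11.10 on what under-dosed patients are excluded from.

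**Cost.** Protocol and SAP wording, using tissue that section 9.4.1 already retains where it was taken. The price is some dilution: with 210 analysed and 10% of B+C under-dosed, power is about 84, 80 or 76% if those patients keep all, half or none of the added effect. Counting pairs may lengthen recruitment slightly.
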